## Abstract

*Background*: Community-based initiatives show promise for preventing childhood obesity. They are characterized by community leaders and members working together to address complex local drivers of energy balance. *Objectives*: To present a protocol for a stepped wedge cluster randomized trial in ten communities in the Great South Coast Region of Victoria, Australia to test whether it is possible to: (1) strengthen community action for childhood obesity prevention, and (2) measure the impact of increased action on risk factors for childhood obesity. *Methods:* The WHO STOPS intervention involves a facilitated community engagement process that: creates an agreed systems map of childhood obesity causes for a community; identifies intervention opportunities through leveraging the dynamic aspects of the system; and, converts these understandings into community-built, systems-oriented action plans. Ten communities will be randomized (1:1) to intervention or control in year one and all communities will be included by year three. The primary outcome is childhood obesity prevalence among grade two (ages 7–8 y), grade four (9–10 y) and grade six (11–12 y) students measured using our established community-led monitoring system (69% school and 93% student participation rate in government and independent schools). An additional group of 13 external communities from other regions of Victoria with no specific interventions will provide an external comparison. These communities will also allow us to assess diffusion of the intervention to control communities during the first three years of the trial. *Conclusion*: This trial will test effectiveness, over a five-year period, of community-owned, -supported and -led strategies designed to address complex and dynamic causes of childhood obesity.

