#### 2.4.2. Primary and Secondary Outcomes

Primary outcome: change in childhood BMI-z and obesity prevalence. Secondary outcomes: change in children’s diet and physical activity (PA) behaviours, community systems, and settings environments for food and PA. The previously published detailed methodology of the sustainable monitoring system is briefly outlined below [17,37].

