### 2.7. Sample Size

Based on school enrolment data, we estimate that there are 5050 children in the GSCRV in grades two, four or six across 84 primary schools in the region. Using an opt-out consent process, which delivers a >90% response rate, and assuming that 75% of schools will participate, we expect to measure more than 3000 children at each study wave meaning 3000 observations at each step and 9000 across the three study data points. BMI-z standard deviation (1.2) and intra-cluster correlation (0.027) were estimated in a previous study of >2500 Victorian school children (2014–2015). Under the stepped wedge design (ten clusters, three data collection points, five clusters) randomized to intervention at step 1, there will be an average of 300 children in each cluster, and the minimum detectable difference in BMI-z between groups with 80% power will be 0.13. This compares favourably with the observed difference achieved in previous successful intervention studies in children of 0.18, which was associated with a 3% reduction in prevalence of overweight and obesity over three years [7,8,9].

While the power for the current study is based on the stepped wedge design alone, the external parallel control group of 13 communities will add an additional comparative power to this trial.

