## 3. Analysis Plan

Social network analysis (SNA) [47] will be used to quantify the strength and importance of relationships among people and organizations who have control over environments that affect children’s health [48]. Social network analysis software (e.g., “SNA” and “network” in R [49] will be used to calculate network statistics for each community including density and centrality and “opinion leader” positions, which are statistics used to identify people in the network who send or receive the most connections to others (the former indicating influence, the latter prominence), or who occupy other central or bridging positions in a network that are important to network diffusion and connecting relatively disconnected areas of the network. Social network dynamics will be modeled using longitudinal network models to determine how the networks change over time, the factors that predict the formation and maintenance of new relationships, and the role of the network in the diffusion information, knowledge and practice. Additional systems measurement will comprise evaluation of change in systems maps, tracking of change in subsystems and process evaluation of the communities’ responses to the systems intervention. The grounded logic models developed through this process will also allow the addition of other data sources, whether bespoke or routine data, for an understanding of the change in systems.

The effect of the intervention on the main outcome (BMI-z) will be assessed using a linear mixed model with cluster as a random effect (community) and time (step), intervention and interaction of time by intervention as fixed effects. Because intervention enrolment will be staggered, data will be analyzed following two different approaches: (1) an intention to treat principle irrespective of when the enrolment effectively occurred; and (2) considering actual enrolment time. Secondary outcomes will be analyzed by fitting a generalized linear mixed model with link and distribution selected according to the variable (Figure 2). Missing outcomes (which we anticipate will be sparse due to the selection criteria “child present at school on the day of data collection”) will be managed using an inverse probability weighting approach.

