**Figure 2 ijerph-13-01143-f002:**
[figure not shown]
Hypothesis testing over time for the WHO STOPS trial.

**Table 1 ijerph-13-01143-t001:** Study design for the WHO STOPS cluster randomized controlled trial.

Community Type	*n*	Baseline	Step 1		Step 2	
Participant communities	5	**^#^ *** (0)	**^#^** (0)	**^#^ *** (0)	**^#^ (1)**	**^#^ * (2)**
	5	**^#^ *** (0)	**^#^ (1)**	**^#^ * (2)**	**^#^ (3)**	**^#^ * (4)**
External control	13	***** (0)	(0)	***** (0)	(0)	***** (0)
Year		2015	2016	2017	2018	2019

**^#^** Data collection systems mapping; ***** Date collection individual outcomes; (X) = Years in intervention group; Data in bold denotes intervention period.

**Table 2 ijerph-13-01143-t002:** Intervention design activities.

Workshop	Content
**3 h Workshop 1** Problem Identification	Background, evidence, plan presentation; fill in community capacity index; develop system logic model for “causes of childhood obesity in their community” (outcomes evidence translation, baseline measurements, base systems model).
**3 hour Workshop 2** Problem Refinement	Further evidence presentation; fill in social network analysis questionnaires; validation of system logic model on contextualised caused of childhood obesity constructed from the previous workshop (outcomes-further baseline data and knowledge translation and first validation of model).
**Half-day Workshop** Solution Formulation and Prioritisation	Steering group recruits between 50 and 200 champions from across the community who validate the systems logia model and identify priority actions for each sub-system (e.g., water system, school system, food system) related to them (outcomes; wider community validation of model and action plans).
**2 h Workshop 2** Solution Integration	Review the consolidated priority actions (outcomes; translate to institutional action plans).
**1–2 h Evaluation****Sessions** Adaptive Solutions	Steering: six monthly sessions to identify subsystem changes and modifications to the systems map (outcomes such as individual child measures, process change; follow up system measures).

**Table 3 ijerph-13-01143-t003:** Primary and secondary outcomes of interests and proposed instruments.

Item	Outcome(s) of Interest	Instrument/Measure
Anthropometry	Body Mass Index-z score	Height and weight
	Overweight and obesity prevalence [37,38]	

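### The primary outcome is named in three incompatible ways, and only BMI-z has a sample size and a primary model behind it

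*Protocol article*

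**What the plan says.** The article answers the question of what is primary in several places, and the answers differ.

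- Abstract: "The primary outcome is childhood obesity prevalence among grade two", four and six students. This is one binary outcome.
- Section 2.4.2: "Primary outcome: change in childhood BMI-z and obesity prevalence". These are two outcomes, one continuous and one binary, with no ranking.
- Section 3: "The effect of the intervention on the main outcome (BMI-z) will be assessed using a linear mixed model". The next outcome sentence reads "Secondary outcomes will be analyzed by fitting a generalized linear mixed model with link and distribution selected according to the variable".
- Section 2.7: "BMI-z standard deviation (1.2) and intra-cluster correlation (0.027) were estimated in a previous study". The detectable difference of 0.13 at 80% power is also in BMI-z units. Prevalence appears only as background: earlier studies saw a BMI-z difference of 0.18 alongside a 3% reduction in overweight and obesity.
- Table 3 covers primary and secondary outcomes together. It lists BMI-z and "Overweight and obesity prevalence" without marking either as primary.

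**The concern.** A confirmatory trial needs its primary outcome fixed before the data are seen. Here a reader of the Abstract would judge the trial on obesity prevalence, a reader of Section 3 on BMI-z, and a reader of Section 2.4.2 on both. If one outcome reached significance and the other did not, the article would support calling the trial positive or negative, depending on the section cited.

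The binary outcome is also loosely defined. The Abstract and Section 2.4.2 say obesity. Table 3 and the background figure in Section 2.7 refer to overweight and obesity. A result could move between these two definitions.

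Finally, the outcome that the Abstract calls primary has no power statement. Section 2.7 sets the detectable 0.13 beside an earlier effect described in both BMI-z and prevalence, so a reader may assume that the prevalence effect is covered as well.

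**Working it through.** **Side by side**

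| Place | Primary or main outcome | Powered? | Model given as primary? |
|---|---|---|---|
| Abstract | obesity prevalence | no | no |
| Section 2.4.2 | BMI-z and obesity prevalence | BMI-z only | BMI-z only |
| Section 2.7 | BMI-z (implied by the calculation) | yes | not applicable |
| Section 3 | BMI-z | yes (Section 2.7) | linear mixed model |

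No reading satisfies the Abstract, Section 2.4.2 and Section 3 at once. The contradiction needs no arithmetic. The calculation below only shows what the choice of outcome does to power.

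**Inputs from the article.** Ten communities, five crossing over at each step, measured in 2015, 2017 and 2019; 300 children per community per wave ("3000 observations at each step and 9000 across the three study data points"); SD 1.2; intra-cluster correlation 0.027; 28% of Australian children overweight or obese (Introduction).

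**Assumed, because the article does not state it.** A 5% significance level, tried one- and two-sided; the BMI-z intra-cluster correlation carried over to the binary outcome; the national 28% applied to the region; the cited 3% read as percentage points.

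**Step 1: reproduce the stated 0.13.** I used the Hussey-Hughes variance with period effects and a random community intercept, for sequences 0-1-1 and 0-0-1.

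- Design sums: I = 10, T = 3, U = 15, W = 5² + 10² = 125, V = 5×2² + 5×1² = 25.
- Within-cluster variance of a cluster-period mean: s = 1.44 × 0.973 / 300 = 0.00467. Between-cluster variance: t = 1.44 × 0.027 = 0.03888.
- Var = I·s·(s + T·t) / [(I·U − W)·s + (U² + I·T·U − T·W − I·V)·t] = 10 × 0.00467 × 0.12131 / (25 × 0.00467 + 50 × 0.03888) = 0.00275, so SE = 0.0524.
- Detectable difference at 80% power: one-sided 5%, (1.645 + 0.842) × 0.0524 = 0.130; two-sided 5%, (1.960 + 0.842) × 0.0524 = 0.147.

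With these inputs the stated 0.13 is matched by a one-sided 5% test. At two-sided 5%, power at 0.13 is 70%.

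**Step 2: BMI-z at the cited 0.18.** Φ(0.18/0.0524 − 1.96) = 93%, two-sided.

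**Step 3: overweight plus obesity.** SD = √(0.28 × 0.72) = 0.449. SE = 0.0524 × 0.449/1.2 = 0.0196, or 1.96 points.

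- Two-sided 5%: Φ(0.03/0.0196 − 1.96) = 33%; detectable difference 5.5 points.
- One-sided 5%: Φ(0.03/0.0196 − 1.645) = 45%; detectable difference 4.9 points.

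**Sensitivity (two-sided 5%, 3-point fall).**

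- Intra-cluster correlation 0.005 to 0.05: 33% to 35%. At zero: 45%.
- Baseline 25%: about 35%. Baseline 40%: about 29%.
- Cluster autocorrelation 0.8 between waves: 16%.
- If 3% is a relative reduction (0.84 points at 28%): about 6%.

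**Step 4: obesity alone.** The article gives neither a rate nor an expected effect. If the rate were 7% to 10%, a 3-point fall would have about 77% to 63% power (two-sided). A 3-point fall would be 30% to 43% of such a rate, and the article does not propose it as a target.

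**The case against.** The strongest reply is that an article condenses a fuller protocol. A success rule for two outcomes and a model for prevalence are commonly left to the analysis plan, and Figure 2 on hypothesis testing is not shown. This stands as far as it goes: the lack of a multiplicity rule is not a fault in itself. It does not remove the point, which is that the article gives conflicting answers. A later document could settle the matter only by overriding at least one of these sections.

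Second, Table 3 should not be overread. Its row label may mean overweight and obesity reported separately, and it names no rival primary outcome. I accept this and use it only to show that the prevalence definition needs stating.

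Third, the calculation invites stronger readings, which the article does not support:

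- A reader might infer that the Abstract's primary outcome has about 33% power, or that the trial cannot test it adequately. But the 28% and the 3% both concern overweight plus obesity, while the Abstract and Section 2.4.2 name obesity. For obesity alone, adequacy is undetermined.
- A reader might treat the 3% as the design target. Section 2.7 mentions it only as what accompanied a BMI-z difference of 0.18, for which power is good.
- A reader might put the false-positive risk at 1 − 0.95² = 9.75%. That assumes two independent tests and an either-counts rule. Both outcomes come from the same height and weight, so independence is implausible, and no such rule is stated.

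**Conclusion.** The contradiction is established on the face of the article and rests on no assumption. Three sections name three different primary outcomes, only BMI-z is powered, and a model suited to a binary outcome is mentioned only for secondary outcomes. The choice of endpoint is therefore open after the data are seen. This should be corrected before analysis.

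The power figures are supporting and conditional. For overweight plus obesity at 28%, with a 3-point absolute fall and an intra-cluster correlation of 0.027, power is about 33% (two-sided) to 45% (one-sided). The match of 0.13 to a one-sided test does not prove that one was intended, because Section 2.7 states neither level nor sidedness. Near a 28% baseline, power for this effect is well below 80% in every variant tried. None of these figures carries over to obesity alone.

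**What to change.** Name BMI-z as the single primary outcome in the Abstract, Section 2.4.2, Section 3 and Table 3, because the sample size and the primary model are already built on it. Possible wording: *The primary outcome is BMI-z. Prevalence of [obesity / overweight plus obesity, by a stated definition] is a secondary outcome, tested only if the BMI-z result is significant.*

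State one definition of prevalence and use it throughout, including in the economic evaluation, which relies on obesity prevalence. If a power figure for prevalence is added, give its baseline, effect, intra-cluster correlation, significance level and sidedness beside it.

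If the investigators want both outcomes to be primary, the alternative is to declare them so, say whether both or either must succeed, and give power for each.

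The recommended change costs wording only and needs no new data. Its price is that prevalence, the outcome featured in the Abstract, moves to a secondary place.

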## 1. Introduction

Obesity is a major determinant of Type 2 diabetes, coronary heart disease, and cancer. In Australia, obesity costs the health system more than $21 billion annually [1] and more than one-quarter (28%) of Australian children are overweight or obese [2]. The size and scope of the burden, together with overweight youth having a 70% chance of becoming obese adults [3], make the case for prevention compelling. Children are a critical focus for prevention because they are so susceptible to the environment and because treatment is difficult. Childhood obesity has been recognized as a priority in the WHO’s Global 2013–2020 Action Plan for the Prevention and Control of Non Communicable Disease [4] and recommendations have been provided to countries on ending childhood obesity [5].

Recent Cochrane meta-analysis of childhood obesity interventions showed an overall benefit for community-based interventions among primary school-aged children [6]. The 55 studies reviewed evaluated mainly small, discrete interventions delivered over the short term and not “scaled up” to population levels. Several successful community-based studies [7,8,9] showed that improving broader system determinants (e.g., community capacity), strongly predicts the degree of reduction in childhood obesity [10]. The 2015 Lancet Obesity Series [11] identified the challenge for community-based childhood obesity prevention initiatives as the creation of sustained, large-scale interventions that work at multiple levels [12].

Several attempts have been made or are underway to work at population scale in Australia (e.g., Healthy Together Victoria), New Zealand [13] and England [14]. These population-level interventions begin by fostering a shared understanding of the systemic determinants of non-communicable disease and asking how existing systems can be strengthened or new systems created to better promote health and prevent disease [15]. One of the clear messages from previously successful trials is that building community capacity to apply systems thinking is critical [10]. Systems thinking is characterized by attempts to identify the most important cause and effect relationships within a specific system boundary that create feedback and so amplify or stabilise change across a system. System dynamics, an approach to systems thinking, explicitly seeks to create informal maps and formal simulation models of this dynamic complexity [16]. While many more traditional interventions have focused on linear cause-and-effect relationships, systems interventions focus on non-linear relationships (e.g., tipping points), feedback where a “causal” variable might in turn be impacted by an “outcome variable”, and complexity in the multilevel factors involved, as well as multiplex relationships among these factors.

New methods are required that facilitate communities’ and researchers’ ability to measure the components and processes of relevant systems (i.e., systems that impact childhood obesity in their community), to map and understand these systems, and to use systems data and models in real time to implement change and make ongoing improvements at multiple levels. Similarly, new methods are required to integrate economic analysis into systems approaches so that cost-effectiveness can be measured.

In this paper, we present the protocol for the Whole of Systems Trial of Prevention Strategies for childhood obesity (WHO STOPS childhood obesity) trial. This trial has grown out of strong partnerships between researchers and community leaders in the Great South Coast Region of Victoria (GSCRV), Australia. Shared work in preparation for this study has included creation of: (1) a sustainable and high participatory obesity-monitoring system; and (2) whole of community systems measures and interventions.

### 1.1. A Sustainable Monitoring System

In 2015, a childhood obesity-monitoring system was established across six local government areas in South-Western Victoria [17]. We used locally sourced competitive funding to conduct training, manage data collection, conduct analysis and support an in-kind contribution from health services, local government and schools to conduct data collection. Anthropometric and behavioural data were collected from 90% of children in 48 of the 84 primary schools in the GSCRV. Partners have committed to provide in-kind support to collect these data again in 2017 and 2019.

### 1.2. Whole of Community Systems Measures and Interventions

The researchers and community leaders have developed and piloted a range of systems action tools and techniques to build community capacity and ownership of efforts to apply system thinking to community-wide childhood obesity prevention.

This paper sets out a protocol for the WHO STOPS Obesity project designed to bring all these lessons together and test the efficacy and cost-effectiveness of the approach for preventing obesity among primary school-aged children in South-Western Victoria, Australia.

The trial is registered by the Australian New Zealand Clinical Trials Registry (ACTRN12616000980437).

## 2. Methods

This is a cluster randomized stepped wedge trial (two steps) in ten communities. The unit of randomisation and intervention is the community (rather than individual children). Following baseline measurement of all eligible children in all ten communities (2015), five communities will be randomized to the intervention in year one (step one) and the remaining five will be entered into the intervention two years later (step two) (Table 1). Grades two, four and six children in all clusters will be measured in the baseline year (2015), year two (2017) and year four (2019). Data collection every second year reflects a more cost-effective measurement approach and a realistic timeframe to begin to see changes in weight status among intervention populations. Opportunities and funding for longer-term data collection (i.e., a five- and ten-year follow up) will be actively sought in due course.

### 2.1. Study Population

The units of observation are all primary school-aged children in grades two, four and six (aged approximately 6 to 12 years) (*n* = 5050) in ten communities of the GSCRV. Clusters, or “natural communities”, are distinct, dispersed population centres agreed by partners based on existing government, health service, and education boundaries (see Figure 1). The ten enrolled clusters will be ranked in order of size, and one community from each quintile will be randomly allocated to intervention at step one. Blinding and allocation concealment is not possible in trials where whole communities are recruited into the design, implementation and evaluation.

This stepped wedge design [18,19] is particularly suited to situations where: randomisation of individuals is not possible (i.e., population level trials); the intervention is expected to be of benefit and unlikely to do any harm (i.e., where previous small-scale interventions have been successful); and, where allocation of communities to a control-only arm would be problematic, unethical, or likely to result in communities refusing to participate [20,21]. The design provides strong analytic qualities, with intervention/control exposure and comparison available both within and across arms [22,23]. The trial described requires intensive support efforts across multiple communities and so it is not feasible to deliver it across all communities simultaneously. It is also designed iteratively so that subsequent communities benefit from lessons learned from the preceding communities.

